**Figure 1 fig1:**
[figure not shown]
Study design and intervention sequence of the randomized crossover trial.

The primary objective of the trial is to determine whether NNPO therapy, as a short-term intervention, is non-inferior to conventional OPEP therapy with respect to sputum clearance.

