### Sample size calculation

The sample size was calculated based on the primary outcome, sputum wet weight, using a non-inferiority design. A non-inferiority margin of 1.5 g was prespecified, as justified above. Variability estimates were obtained from a preliminary pilot study, which indicated a within-subject standard deviation of approximately *σ* g for wet sputum weight following airway clearance interventions.

Assuming a true mean difference of 0 g between NNPO and OPEP, a one-sided significance level (*α*) of 0.025, and 80% power, a minimum of 38 participants was required to demonstrate non-inferiority in this crossover study. To allow for potential dropouts or incomplete data, the target sample size was increased to 42 participants.

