## Statistical analysis

All statistical analyses will be performed using R software (version 4.3; R Foundation for Statistical Computing, Vienna, Austria). Normality of continuous variables will be assessed using the Shapiro–Wilk test. Normally distributed variables will be presented as mean ± standard deviation (SD), while non-normally distributed variables will be reported as median (interquartile range, IQR). Categorical variables will be summarized as counts and percentages.

Between-treatment differences in wet sputum weight will be analyzed using linear mixed-effects models (LMMs), with treatment group as a fixed effect and participant as a random effect. In the absence of a statistically significant difference, a non-inferiority analysis will be performed comparing NNPO therapy with OPEP therapy. The non-inferiority margin is set at 1.5 g. As no established margin exists for short-term wet sputum weight, this threshold was determined *a priori* based on evidence suggesting a clinically meaningful 24-h sputum weight change of approximately 6.4 g following airway clearance interventions (16), combined with pilot data demonstrating minimal between-treatment differences. Non-inferiority will be concluded if the lower bound of the 95% confidence interval (CI) for the NNPO–OPEP difference exceeds −1.5 g.

Lung function parameters and oxygenation (SpO₂/FiO₂) will also be analyzed using LMMs to assess pre–post intervention changes and treatment-by-time interactions. Change scores (*Δ*) will be calculated and compared between interventions.

Patient-reported outcomes, including perceived efficacy and comfort, will be compared using independent-samples t-tests or Mann–Whitney U tests, as appropriate. All statistical tests will be two-sided unless otherwise specified. A *p* value < 0.05 will be considered statistically significant, except for the non-inferiority analysis of wet sputum weight, which will use a one-sided significance level of 0.025.

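### The non-inferiority analysis is run only after a non-significant difference test, which conflicts with the primary objective and with the plan's own confidence-interval rule

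*Protocol article*

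**What the plan says.** Under Trial design, the protocol article calls the study a non-inferiority trial and, below Figure 1, states: "The primary objective of the trial is to determine whether NNPO therapy, as a short-term intervention, is non-inferior to conventional OPEP therapy". The Sample size calculation section sizes the trial for one non-inferiority test: margin 1.5 g, true difference 0 g, one-sided alpha 0.025, 80% power, at least 38 participants, raised to 42 for dropout. It does not mention any preceding test.

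The Statistical analysis section first compares wet sputum weight between treatments in a linear mixed model and then says: "In the absence of a statistically significant difference, a non-inferiority analysis will be performed comparing NNPO therapy with OPEP therapy". The preceding test is two-sided at 5% ("All statistical tests will be two-sided unless otherwise specified"; "value < 0.05 will be considered statistically significant"). A few sentences later comes the decision rule: "Non-inferiority will be concluded if the lower bound of the 95% confidence interval (CI) for the NNPO–OPEP difference exceeds −1.5 g". For the non-inferiority analysis the level is set separately ("which will use a one-sided significance level of 0.025").

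The section does not say what is concluded about non-inferiority when the difference is significant, in either direction.

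**The concern.** The primary question should be tested in every trial outcome. As written, it is tested only in some, and a test that is not the primary one decides which. Two situations follow.

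- **NNPO significantly better.** The condition is not met, so the non-inferiority analysis is not performed, although the result answers the primary question more strongly than non-inferiority would. The Discussion treats non-inferiority and superiority both as possible favourable results, so this outcome is within the plan's sights.
- **NNPO significantly worse, but with the whole interval above −1.5 g.** The decision rule says non-inferior, while the conditional sentence says the analysis is not done. The plan does not say which sentence governs.

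What is at stake is a clear primary conclusion. If one of these outcomes occurs, someone must choose between two conflicting sentences after seeing the data.

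**Working it through.** **Inputs.** Margin 1.5 g, one-sided alpha 0.025, power 80%, true difference 0 g and N = 38 (Sample size calculation); two-sided 5% for the difference test and the lower-limit rule (Statistical analysis). The within-subject SD is printed only as a symbol, so 38 cannot be reproduced forwards. It is not needed here, because 80% power at a true difference of 0 fixes the standard error. A normal approximation is used.

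**Step 1: implied precision.**
SE = 1.5 / (1.960 + 0.8416) = 0.535 g.
With N = 38 this corresponds to an SD of within-participant differences of 0.535 × √38 ≈ 3.30 g.

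**Step 2: the two rules, in terms of the estimate d (NNPO minus OPEP).**
- Margin rule met: d > −1.5 + 1.96 × 0.535 = −0.451 g.
- Difference not significant: −1.049 g < d < 1.049 g.
- Both, as the literal text requires: −0.451 g < d < 1.049 g.

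**Step 3: at the design assumption (true difference 0 g).**
- Margin rule alone: P(Z > −0.8416) = 80.0%, which reproduces the stated power.
- Literal procedure: P(−0.8416 < Z < 1.96) = 0.975 − 0.200 = 77.5%.
- The missing 2.5 points are P(Z > 1.96), the trials in which NNPO is significantly better. In each of these the lower limit is above 0 and so above −1.5 g.

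**Step 4: other true differences, same SE.**

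| True difference | Primary test not run | Formal non-inferiority, literal text | Margin rule alone | NNPO significantly better |
|---|---|---|---|---|
| 0 g | 5.0% | 77.5% | 80.0% | 2.5% |
| +0.5 g | 15.4% | 81.0% | 96.2% | 15.2% |
| +1.0 g | 46.3% | 53.3% | 99.7% | 46.3% |
| +1.5 g | 80.0% | 20.0% | 100.0% | 80.0% |

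In every row the gap between the two non-inferiority columns equals the last column, up to rounding.

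**Step 5: with all 42 evaluable and the same SD.** At 0 g the margin rule alone gives 83.8% and the literal procedure 81.3%.

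**Step 6: type I error.** At a true difference of −1.5 g both versions conclude non-inferiority with probability 2.5%.

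**Step 7: significantly worse but within the margin.** This needs −1.5 + 1.96 × SE < d < −1.96 × SE, which is possible only if SE < 1.5 / 3.92 = 0.383 g (SD of differences below about 2.36 g at N = 38). At 0.535 g the two limits are −0.451 and −1.049, so the set is empty; in a t-based simulation its frequency was below 0.01%. Two illustrations with smaller SEs, both assumptions:
- SE = 0.535 / √2 = 0.379 g: the window runs from −0.758 to −0.742 g, about 0.016 g wide. It is hit with probability about 0.2% at a true difference of 0 and under 2% at −0.75 g.
- SD of differences 2.0 g, N = 38, true difference −0.5 g: probability about 21%.

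**The case against.** The strongest reply is that the condition does little harm in practice. Where NNPO is significantly better, the same interval already satisfies the margin rule, and that rule is worded without a condition; a sensible analyst would report NNPO as at least non-inferior. Where the condition is met, the lower limit must still exceed −1.5 g. The condition can therefore withhold a claim but never create one. With the margin fixed in advance and both conclusions read from one interval, looking at the difference first causes no error inflation.

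Most of this stands, and it rules out three stronger readings that a reader might infer.

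- *That the trial does not deliver its 80% power.* The shortfall at 0 g is 2.5 points, consists wholly of trials favouring NNPO, and disappears once those are counted as successes. Even literally, power is 81.3% if all 42 are evaluable. The wide gaps at +0.5 g and +1.0 g are likewise superiority results that lose a label, not failures to show that NNPO is no worse.
- *That a non-significant difference is being taken as proof of similarity.* It is not; the margin rule still has to be met at one-sided 0.025.
- *That a result worse than OPEP but within the margin is a likely casualty.* It cannot arise at the planned SE under the normal approximation. Assuming that two sessions per device shrink the SE by √2 is not supported, because the article does not say whether 38 already reflects both sessions.

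What the reply does not remove is the conflict itself. The benign reading has to be supplied by the reader, and it does not settle the case of an interval wholly between −1.5 g and 0. That case cannot be excluded, because the SD has no printed value.

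**Conclusion.** The point holds as an error in the stated decision procedure. The plan makes its primary analysis conditional on a test that the objective, the sample size and the margin rule do not call for, and it leaves the primary conclusion undefined when that test is significant.

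The practical loss is modest. Under the literal text the primary test goes unrun in 5.0% of trials at the design assumption, and more often the better NNPO truly is. Recoverable power is unchanged at 80.0%, and the false-positive risk stays at 2.5%. These figures rest on a normal approximation and on an SE consistent with 80% power at N = 38. The conflict over a significantly worse result within the margin is a gap in the rule that would matter only if precision turned out clearly better than planned (SE below about 0.383 g).

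It should still be corrected, because the repair is trivial beforehand and a choice between the two sentences after the data are seen would weaken the primary conclusion.

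**What to change.** In Statistical analysis, delete the condition and state a fixed order:

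1. Primary analysis, always performed: compare the lower limit of the two-sided 95% confidence interval for NNPO minus OPEP with −1.5 g. Non-inferiority is concluded if the limit is above −1.5 g.
2. Only if step 1 is met: conclude superiority if the lower limit of the same interval is above 0. No alpha adjustment is needed.

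Add that an interval wholly between −1.5 g and 0 is reported as meeting the margin, with the significant difference in favour of OPEP stated alongside.

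The cost is a sentence or two in the protocol or analysis plan, with no extra participants, data or visits. It should be dated before the treatment comparison is seen.

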### Trial design

This prospective, multicenter, randomized, crossover, non-inferiority trial aims to evaluate the efficacy of a novel airway clearance technique, nasal negative pressure oscillatory (NNPO) therapy, in hospitalized patients. The protocol is developed and reported in accordance with the SPIRIT 2025 guidelines (15). To minimize inter-individual variability in sputum production and airway clearance capacity, a self-controlled crossover design is employed, with each participant receiving both interventions and serving as their own control. NNPO therapy is compared with conventional airway clearance using oscillatory positive expiratory pressure (OPEP).

The study is conducted over a continuous 4-day intervention period. Participants receive one intervention on Days 1 and 3 and the alternate intervention on Days 2 and 4. Two treatment sequences are predefined: Sequence A, in which NNPO is administered on Day 1 followed by OPEP on Day 2, and Sequence B, in which OPEP is administered on Day 1 followed by NNPO on Day 2. The same intervention sequence is repeated on Days 3 and 4 to enhance the reliability of treatment comparisons. Allocation to Sequence A or Sequence B is performed using a computer-generated randomization schedule (Figure 1).

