### Outcomes and assessment schedule

The primary outcome was sputum wet weight, collected during each treatment session and for up to 30 min after session completion. Sputum was collected into pre-weighed, sealed sterile containers and immediately weighed using a calibrated electronic scale. Collection was performed using a standardized procedure under the supervision of study personnel throughout the airway clearance process. During collection, participants were instructed to avoid swallowing sputum when present and to expectorate it promptly for collection. Study personnel made real-time judgments based on the pattern of expectoration and avoided collecting secretions following throat clearing or intentional saliva generation. For participants with viscous oral secretions that might increase the risk of saliva contamination, mouth rinsing with water was permitted prior to treatment to reduce oral contamination.

Secondary outcomes include: (1) Lung function—FEV₁, FVC, FEV₁/FVC, MEF₇₅, MEF₅₀, MEF₂₅, and MMEF₇₅/₂₅—measured before and 30 min after each daily treatment session. Lung function parameters were assessed using a respiratory rehabilitation device (PE100, e-Linkcare Meditech Co., Ltd.); (2) peripheral oxygen saturation (SpO₂/FiO₂) measured at rest before treatment, during the final minute of each session, and 30 min post-treatment; (3) patient-reported treatment efficacy and comfort assessed using 10-cm visual analogue scales after completion of all treatment days; and (4) the incidence of adverse events during or immediately after each session (Table 2).

**Table 2 tab2:** Assessment schedule for primary and secondary outcomes.

Outcome	Time points of assessment
Sputum wet weight (g)	Collected during each treatment session and up to 30 min post-intervention
Lung function (FEV1, FVC, FEV1/FVC, MEF75, MEF50, MEF25, MMEF75/25)	Measured immediately before each daily treatment session and 30 min after completion
Peripheral oxygen saturation (SpO₂/FiO₂)	Recorded at baseline (pre-treatment), during the final minute of the session, and 30 min post-treatment
Patient-reported treatment efficacy (VAS 0–10)	Assessed after completion of all daily treatment sessions
Patient-reported comfort (VAS 0–10)	Assessed after completion of all daily treatment sessions
Adverse events	Monitored during and immediately following each treatment session

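### Lung function and SpO₂/FiO₂ get two unranked tests of the same pre-post contrast; one baseline-adjusted model per outcome would be clearer and more precise

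*Protocol article*

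**What the plan says.** Under Trial design, each participant has four sessions, two per device: "Participants receive one intervention on Days 1 and 3 and the alternate intervention on Days 2 and 4". Under Outcomes and assessment schedule, lung function is "measured before and 30 min after each daily treatment session", so each session yields its own pair of values. SpO₂/FiO₂ has three readings per session: "measured at rest before treatment, during the final minute of each session, and 30 min post-treatment".

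The Statistical analysis section writes out one mixed-model structure, for wet sputum weight: "with treatment group as a fixed effect and participant as a random effect". The next paragraph says that lung function and oxygenation will "also be analyzed using LMMs to assess pre–post intervention changes and treatment-by-time interactions". The sentence after it adds that change scores "will be calculated and compared between interventions". Apart from the non-inferiority test, the significance rule is the same throughout: a p "value < 0.05 will be considered statistically significant".

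For these secondary outcomes the section does not state the random effects, the method for comparing change scores, any covariate, or which of the two analyses carries the conclusion.

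**The concern.** Two tests are committed to for one question, at the same threshold and with no order between them. If their standard errors differ, one estimate can come out significant in one test and not in the other, and the choice between them would be made after seeing the data.

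The standard errors will differ if the secondary model has participant as its only random effect. A patient in an exacerbation has better and worse days, and a session's pre and post values share that day's level. A change score cancels the shared part. A participant-only model leaves most of it in the residual, which widens the interval for the interaction.

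The pre-session value is also available as a covariate, and the text does not mention using it that way. At stake is precision on the effect on pulmonary function, which Trial objectives lists among the secondary aims, and on oxygenation. An interval wider than it need be could hide a real difference between devices.

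**Working it through.** The plan states no figure for these analyses, so there is none to reproduce. The check is of what each stated analysis does.

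**Inputs.** From the protocol article: 4 sessions per participant, 2 per device; 2 lung-function readings per session; at least 38 participants (Sample size calculation). Assumed: r, the correlation of pre and post values in the same session within a participant. The documents do not give it, so a range is shown.

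**Model for the check.** Value = participant effect + session effect (variance s²) + error (variance e²), with pre and post equally variable within participants. Then r = s²/(s² + e²).

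**Step 1: same estimate.** With two time points and complete data, the treatment-by-time coefficient is (mean post − mean pre under NNPO) − (mean post − mean pre under OPEP). That is also the difference in mean change scores. In simulated data sets the two agreed to rounding error. Only the standard error can differ.

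**Step 2: standard error if participant is the only random effect.** The true error of the interaction depends on e² alone, because s cancels in each change. The participant-only model uses a residual variance of about s² + e². The ratio of standard errors is √((s² + e²)/e²) = 1/√(1−r).

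| r | SE ratio | Real size of a nominal 0.05 test | Simulated size |
|---|---|---|---|
| 0.3 | 1/√0.7 = 1.20 | 0.019 | 0.024 |
| 0.5 | 1/√0.5 = 1.41 | 0.006 | 0.010 |
| 0.7 | 1/√0.3 = 1.83 | 0.0004 | 0.001 |

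The simulated column used 38 participants and 2,000 runs per r. It is slightly less extreme because 1/√(1−r) is an upper limit. With only four sessions, the participant effect absorbs part of the session variation. Per participant, the within-participant sum of squares has expectation 3(2s² + e²) + 4e² = 6s² + 7e² on 7 degrees of freedom, so the residual variance is e² + (6/7)s². The ratio becomes √(1 + (6/7)·r/(1−r)): 1.17 at r = 0.3, 1.36 at 0.5 and 1.73 at 0.7. The conclusion does not change.

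**Step 3: cost in power.** In a simulation with 40 participants and 3,000 runs per r, the effect was set so that the change-score test had 80% power. The participant-only interaction test had 76% at r = 0.2, 56% at r = 0.5 and 10% at r = 0.8.

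**Step 4: validity of the change score.** Compared at participant level, its simulated type I error was 0.044 to 0.060 for r from 0 to 0.9. It is valid.

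**Step 5: change score against covariate adjustment.** Within participants, with unit variance, the change has variance 2(1−r) and the post value given the pre value has variance 1−r². The ratio is (1−r²)/(2(1−r)) = (1+r)/2.

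| r | Variance ratio | Reduction |
|---|---|---|
| 0.3 | 0.65 | 35% |
| 0.5 | 0.75 | 25% |
| 0.7 | 0.85 | 15% |
| 0.8 | 0.90 | 10% |

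**Step 6: SpO₂/FiO₂.** Three readings allow two changes from the pre-session value, to the final minute and to 30 min after. The text does not say which one Δ denotes.

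**The case against.** The strongest reply is that the participant-only structure is never stated for these outcomes. It is written for sputum weight, which has one value per session, and it cannot carry over unchanged because a treatment-by-time model needs at least a time term and its interaction. Random effects for secondary outcomes are also detail that an article may leave to the full protocol or SAP. This stands, and it makes the standard-error inflation conditional.

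Second, a reader might infer that the plan uses unadjusted change scores and wastes the pre-session value. The documents do not support that. No method is named for the comparison, so adjustment is not excluded. A change score does use the pre-session value, with a coefficient fixed at 1, and so removes the session effect.

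Third, a reader might infer that the confidence intervals are wrong. That does not follow either. Change-score intervals are valid, and a participant-only interaction would err only by being too wide.

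Fourth, the two inefficiencies are not large together. High r gives a large inflation but little gain from adjustment; low r gives the reverse. Choosing between change scores and covariate adjustment is a choice between valid methods. With no washout, the pre-session values on Days 2–4 are taken after the other device has been used.

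What remains is in the text itself: two tests of one contrast, neither ranked, with neither a session term nor a pre-session covariate mentioned.

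**Conclusion.** The point holds as a low-cost improvement to secondary analyses. Two analyses of the same contrast are planned without saying which is decisive, and for SpO₂/FiO₂ the change itself is not defined.

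The size depends on r, which is an assumption throughout. If participant is the sole random effect in the interaction model, its standard error is inflated by up to 1.20, 1.41 or 1.83 times at r = 0.3, 0.5 or 0.7, with loss of power and no excess of false positives. If the model has a session term, then with two time points and complete data the interaction test coincides with the change-score comparison and this part of the point falls away. In either case, adjusting for the pre-session value gives a variance of (1+r)/2 of the change-score variance, assuming equal within-participant variance before and after the session.

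The non-inferiority conclusion on sputum weight is not touched.

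**What to change.** Name one decisive model per outcome. Regress the 30-min post-session value on treatment, day and that session's pre-session value, with a participant random effect. Split the pre-session value into the participant's mean and the daily deviation from it, so that differences between participants do not set the coefficient used within participants. For SpO₂/FiO₂, fit the final-minute and 30-min values separately, which also settles which change is meant. Report the adjusted NNPO–OPEP difference with its 95% CI.

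Keep the unadjusted change-score difference as a sensitivity analysis, because Days 2–4 pre-session values follow the other device. If the treatment-by-time model is retained, add a session-within-participant random effect to it.

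The cost is analysis wording only. No new data are needed, since every pre-session value is already scheduled.

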## Intervention

Participants received both interventions according to a randomized crossover sequence, with each supervised session performed once daily in the morning.

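### Patient-reported efficacy and comfort are to be compared with independent-samples tests in a crossover where every participant receives both devices, so the nominal 5% level is wrong unless the two ratings are uncorrelated (secondary outcomes only)

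*Protocol article*

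**What the plan says.** The design is paired. The Trial design section describes a self-controlled crossover, "with each participant receiving both interventions and serving as their own control", and sets the schedule: "Participants receive one intervention on Days 1 and 3 and the alternate intervention on Days 2 and 4". The Intervention section repeats it: "Participants received both interventions according to a randomized crossover sequence".

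On the ratings, Outcomes and assessment schedule lists "patient-reported treatment efficacy and comfort assessed using 10-cm visual analogue scales after completion of all treatment days". By then a participant who has completed the schedule has used both devices. The article does not say in so many words how many marks each participant makes.

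On the analysis, the Statistical analysis section says: "Patient-reported outcomes, including perceived efficacy and comfort, will be compared using independent-samples t-tests". The sentence goes on to offer Mann–Whitney U tests as the alternative, as appropriate. Sidedness follows from the general rule in the same section, "All statistical tests will be two-sided unless otherwise specified", with p < 0.05 as the threshold. That section also gives sputum weight a model with a participant random effect, and uses linear mixed-effects models for lung function and oxygenation. Only the patient-reported outcomes get tests for separate groups.

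**The concern.** An independent-samples t-test and a Mann–Whitney U test both assume that the two sets of scores come from different people. Here they come from the same people, and two ratings by one person are usually correlated. The standard error behind the unpaired test is then wrong: too large if people who rate one device high tend to rate the other high as well, and too small if they rate by contrast, favouring one and marking down the other.

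At stake is the evidence on patient acceptance. The Trial objectives section names acceptance of NNPO as a secondary objective, and the efficacy and comfort ratings are its direct measures in Table 2. The Discussion presents NNPO as useful for patients who find conventional techniques uncomfortable or tiring, which a comfort comparison would be used to support.

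**Working it through.** **Inputs from the article.** Every participant receives both devices (Trial design; Intervention). The test is an independent-samples t-test or Mann–Whitney U, two-sided, at 0.05 (Statistical analysis). The minimum number of participants is 38 and the target is 42 (Sample size calculation). The article gives no power, SD or expected difference for the ratings, so there is no figure of its own to reproduce on this point.

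**Assumptions.** One rating per device per participant, equal SD σ for the two devices, normal scores, within-person correlation ρ from −0.3 to 0.7, and a true difference of 0.5σ for power. None of these is in the article.

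**Standard error.** For the mean NNPO − OPEP difference over n participants:

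- assumed by the unpaired test: √(2σ²/n)
- actual: √(2σ²(1 − ρ)/n)
- ratio of assumed to actual: 1/√(1 − ρ), which is 1.20 at ρ = 0.3, 1.41 at 0.5 and 1.83 at 0.7

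**Actual two-sided error at nominal 5%.** In large samples this is 2 × [1 − Φ(1.96/√(1 − ρ))]:

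- ρ = 0.3: 1.96/√0.7 = 2.34, error 1.9%
- ρ = 0.5: 1.96/√0.5 = 2.77, error 0.6%
- ρ = −0.3: 1.96/√1.3 = 1.72, error 8.6%

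**Simulation check.** Correlated normal pairs, 40,000 runs per setting for the t-tests:

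| n | ρ | Error, unpaired | Error, paired | Power at 0.5 SD, unpaired | Power at 0.5 SD, paired |
|---|---|---|---|---|---|
| 38 | −0.3 | 8.5% | 5.1% | 56% | 46% |
| 38 | 0 | 5.1% | 5.0% | 57% | 56% |
| 38 | 0.3 | 2.0% | 5.0% | 59% | 72% |
| 38 | 0.5 | 0.6% | 4.8% | 60% | 85% |
| 38 | 0.7 | 0.06% | 5.0% | 63% | 97% |
| 42 | 0.3 | 2.1% | 5.2% | 64% | 76% |
| 42 | 0.5 | 0.6% | 5.1% | 67% | 89% |
| 42 | 0.7 | 0.05% | 5.1% | 70% | 98% |

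The simulated errors agree with the formula. At ρ = −0.3 the unpaired test rejects more often under the alternative, but only because its error is above 5%.

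The rank tests behave the same way. At n = 38 and ρ = 0.5, Mann–Whitney has an error of 0.7% (10,000 runs) and Wilcoxon signed-rank 4.8% (3,000 runs); their power is 57% and 84%.

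**If only one overall score were taken per person.** That score could not be assigned to a device. Splitting participants into two independent groups would then compare Sequence A with Sequence B, not NNPO with OPEP. The named test fails to answer the question on this reading too.

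**The case against.** The strongest reply is that the article never states that each participant gives one score per device. That is true, and it is treated here as an inference from the crossover and the planned comparison. It does not rescue the test, because the single-score reading leaves no device comparison at all.

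A second reply is that the phrase allowing a choice as appropriate leaves room for a paired test. It does not: the choice offered is between two unpaired tests. Nor is this a detail left to a fuller plan, since the article names the tests.

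A third reply is that the outcomes are secondary and that, with positive correlation, the planned test errs on the cautious side. Both statements are correct and limit the weight of the point. They do not make the p-values right.

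Three stronger readings are tempting, and the document does not support them:

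- **That power is certainly lost.** This needs a positive correlation. At zero correlation the two tests nearly agree; at a negative one the problem is excess false positives. The article gives no correlation.
- **That rating at the end biases the comparison through recall or recency.** One rating occasion after experience of both devices is a legitimate design. The last device is OPEP in Sequence A and NNPO in Sequence B, but allocation to sequence is 1:1, so a simple last-device effect roughly balances in the mean difference. Table 2 also words the timing less clearly than the text, referring to completion of all daily sessions.
- **That the trial's main conclusion is affected.** Sputum weight is analysed with a participant random effect, and the sample size rests on sputum weight alone.

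**Conclusion.** Wrong as written, for the two patient-reported secondary outcomes only. The named tests do not fit the stated design, and nothing else in the article repairs them. That the level is wrong whenever the two ratings are correlated does not depend on the assumed values. Its size does: the actual error is about 2% at a correlation of 0.3, 0.6% at 0.5 and 8.6% at −0.3. With positive correlations of 0.3 to 0.7, 38 participants and a 0.5 SD difference, the planned t-test gives up about 13 to 34 percentage points of power (59% against 72%, up to 63% against 97%). These figures are illustrative, because the article gives neither a correlation nor a rating SD or expected difference.

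**What to change.** Make two changes to the text, before the ratings are analysed.

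1. In Outcomes and assessment schedule, state that each participant rates efficacy and comfort separately for NNPO and for OPEP.
2. In Statistical analysis, replace the independent-samples tests with a paired t-test or Wilcoxon signed-rank test on the within-participant NNPO − OPEP difference. Alternatively, use a mixed model with treatment and sequence as fixed effects and participant as a random effect. This is not identical to the planned sputum model, whose only fixed effect is treatment.

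The paired tests are the safer choice if contrast ratings are thought likely, since a random-intercept model cannot represent a negative within-person correlation.

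The cost is about one sentence in each section. If the rating form already has one mark per device, data collection does not change. The rating schedule, the primary analysis and the sample size can stay as they are.
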